## **1 Aim of the study**

To determine the effectiveness of 14 days nutritional supplementation (RUTF or MNP) given concurrently with the appropriate medical treatment, amongst children diagnosed with malaria and/or diarrhoea and/or LRTI in reducing the incidence of acute malnutrition and the incidence of the 3 study diseases compared to a control group.

### **1.1 Primary objective**

The primary objective is to determine the effectiveness of 14 days of RUTF supplementation versus no supplementation (control group) on the incidence of acute malnutrition

### **Primary Hypothesis**

Supplementation for 14 days with RUTF, concurrently with appropriate medical treatment for malaria, and/or LRTI, and/or diarrhoea reduces the incidence of acute malnutrition compared to a control group during 6 months follow-up, amongst children 6-59 months of age with malaria and/or, LRTI and/or diarrhoea at time of recruitment.

### **1.2 Secondary objectives**

Secondary objectives include the following.

- Incidence of malnutrition

Determine the efficacy of 14 days MNP supplementation versus a control group and RUTF versus MNP on the incidence of acute malnutrition during 6 months follow-up,

- Frequency of morbidity

Determine the effect of 14 days supplementation on the frequency of morbidity (3 study diseases) during 6 months follow-up, comparing both intervention groups to the control group and comparing RUTF to MNP)

- Weight changes immediately after intervention period, measured at day-14 and day-28

Measure mean weight change (total change and rate (grams/kg/day) of change), comparing both intervention groups separately (RUTF and MNP) to the control group

Determine frequency of 'no weight gain and/or weight loss', comparing both intervention groups separately (RUTF and MNP) to the control group

Assess if provision of 14 days of RUTF or MNP supplement promotes a sustained weight gain, measured after 28-days of follow-up, comparing both intervention groups separately (RUTF and MNP) to the control group

- Evaluation of several subgroup to assess potential effect modifiers.

## **2 Study design**

This is a partially blinded randomized controlled trial with three study groups. Children 6 to 59 months of age presenting at the OPD in Goronyo and diagnosed with one or more of the three study diseases (malaria, diarrhoea and LRTI) are eligible for the study.

Children participating in this study will be randomised to one of 3 study groups to:

- A) Receive 14 days of RUTF supplementation with standard care and treatment or
- B) Receive 14 days MNP supplementation with standard care and treatment or
- C) Be included in a control group receiving standard care and treatment but not receiving nutritional supplementation (control group)

Individual follow-up will be 6 months. During this time, children in the RUTF or MNP group will receive 14 days nutritional supplement every time diagnosed with at least one of the three study diseases, not exceeding more than 14 days supplementation in any 28 day period.

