#### **3.2 Secondary endpoints**

Secondary endpoints include

- Number of NNO’s per study group in a period of 6 months
- Time to NNO
- Number of new events of a study disease in 6 months
- Weight change at 14 days and 28 days after study inclusion, and at end of study period
- Rate of weight change (grams/kg/day) at 14 days and 28 days after study inclusion, and at end of study period
- Proportion of children not gaining weight (including losing weight), measured at day-14 and day-28 after study inclusion.
- Proportion of children developing bilateral oedema, overall and per month
- Proportion of moderate acutely malnourished children improving to a non acutely malnourished state, overall and per month
- Mortality: overall mortality
- Morbidity, including the three study diseases (proportion of children with newly diagnosed diseases), overall and per month
- Proportion of children with a reported cough at clinical visit, overall and per month
- Proportion appetite categories
- Proportion and time pattern of children who were breast-fed at baseline and stopped being breast-fed during the study

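### The diagnosis that releases a further supplement course is also the counted morbidity outcome, so morbidity comparisons with control may be biased against the supplements, and the SAP plans no analysis that would show it

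*SAP*

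**What the plan says.** - **Trigger.** Section 2 says that a child in the RUTF or MNP group "will receive 14 days nutritional supplement every time diagnosed with at least one of the three study diseases". The same sentence sets a cap: "not exceeding more than 14 days supplementation in any 28 day period". Controls have standard care and treatment without a supplement.
- **Masking and follow-up.** Section 2 also states: "This is a partially blinded randomized controlled trial with three study groups". It does not say who is masked. "Individual follow-up will be 6 months".
- **Objective.** Section 1 puts the incidence of the three study diseases in the aim, beside acute malnutrition. Section 1.2 has as a secondary objective: "Determine the effect of 14 days supplementation on the frequency of morbidity (3 study diseases) during 6 months follow-up". It covers each supplement against control, and RUTF against MNP.
- **Endpoints.** Section 3.2 lists "Number of new events of a study disease in 6 months" and "Morbidity, including the three study diseases (proportion of children with newly diagnosed diseases), overall and per month".
- **Analysis.** Section 5.5 compares secondary endpoints between arms as in 5.4.1, treats the p-values as exploratory, and allows extra adjustment where baseline characteristics differ. Section 4.2 shows that scheduled visits exist. Neither 3.2 nor 5.5 says whether morbidity events come from scheduled visits, self-initiated visits or both.

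**The concern.** In two of the three arms, the recorded diagnosis does two jobs: it releases a further supplement course, and it is the outcome being counted. In the control arm it is only the outcome. A carer whose child stands to receive a supplement has a reason to bring a mild illness to the clinic that a control carer lacks.

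If that happens, the observed ratio of diagnoses mixes the true ratio of illness with the ratio of the chances that an illness is presented and diagnosed. A real reduction in morbidity could be diluted, hidden, or shown as an apparent excess. A larger sample would only tighten the interval around the distorted value. Randomisation and baseline adjustment do not help, because the difference in attendance arises after allocation and because of it.

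What is at stake is the morbidity part of the stated aim.

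**Working it through.** The SAP gives no morbidity rate, attendance rate or power figure for these endpoints, so there is no stated figure to reproduce. What follows is sensitivity arithmetic.

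**1. How far the cap limits the incentive.** Inputs from section 2: 14-day courses, at most 14 days in any 28, and 6 months of follow-up, taken here as about 182 days. Courses could start on days 0, 28, 56, 84, 112, 140 and 168. That is at most 7 courses: one at enrolment and up to 6 repeats. The cap reduces the incentive, since a child who has just finished a course gains no further full course until the window allows, but it does not remove it.

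**2. The event rate.** Let *a* be the ratio, supplement arm to control, of the chance that an episode is brought to the clinic and diagnosed. Let *s* be the share of control-arm counted episodes found at scheduled visits, where no differential is assumed. Both are assumptions. Then

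observed rate ratio = true rate ratio × [*s* + (1 − *s*) × *a*].

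With all episodes self-presented (*s* = 0) and a true ratio of 0.90:

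- *a* = 1.05 (for example 63% against 60% of episodes presented): 0.90 × 1.05 = 0.945
- *a* = 1.10 (66% against 60%): 0.90 × 1.10 = 0.99
- *a* = 1.20 (72% against 60%): 0.90 × 1.20 = 1.08

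The value of *a* that hides the effect completely at *s* = 0 is 1 / true ratio: 1 / 0.90 = 1.11 and 1 / 0.80 = 1.25.

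With a true ratio of 0.80, the observed ratio is:

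| *s* | *a* = 1.1 | *a* = 1.2 | *a* = 1.5 |
|---|---|---|---|
| 0 | 0.88 | 0.96 | 1.20 |
| 0.5 | 0.84 | 0.88 | 1.00 |
| 1 | 0.80 | 0.80 | 0.80 |

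With no true effect and *s* = 0, the apparent ratio equals *a*, so 1.1 to 1.5 would look like harm. At *s* = 0.5 the same values of *a* give 1.05 to 1.25.

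**3. The proportion with a new diagnosis.** Assume Poisson counts with a mean of 1 recorded episode per control child, and *s* = 0. The control proportion is 1 − exp(−1) = 63.2%. With a true ratio of 0.80 and no differential, the supplement arm shows 1 − exp(−0.80) = 55.1%. With *a* = 1.25 it shows 1 − exp(−0.80 × 1.25) = 63.2%, so the difference vanishes. With *a* = 1.5 it shows 1 − exp(−1.20) = 69.9%. Both morbidity endpoints are exposed in the same way.

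**4. Whether the planned analysis would detect or correct this.** The only adjustment in 5.5 is for baseline characteristics. Attendance is a consequence of allocation, so no baseline covariate carries it. The SAP plans no comparison of attendance by arm and no analysis by visit type.

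**The case against.** **These are secondary, exploratory analyses, and the primary endpoint is nutritional.** This stands, and it limits the weight of the point. It does not make the estimates unbiased, and morbidity is named in the aim.

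**Repeat supplementation at illness is the strategy under test, and the protocol may define ascertainment and masking.** Both stand. The supplement rule is not criticised here. But the choice of analysis belongs to the SAP, and 5.5 fixes none that uses visit type.

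**Scheduled-visit diagnoses are a poor replacement endpoint.** This also stands. For acute, treatable illness they are closer to point prevalence than to frequency over 6 months. They may favour arms in which illness is treated earlier between visits, and a scheduled-visit diagnosis can release a course too. They therefore suit a sensitivity analysis, not the main comparison.

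A reader might infer stronger claims that the SAP does not support:

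- *That bias is established.* There are no attendance or diagnosis rates; the direction is an expectation and the size is unknown.
- *That every diagnosis brings a supplement and controls get nothing.* The 28-day cap applies, and controls receive standard care and treatment.
- *That staff who know the arm record more qualifying diagnoses.* The SAP does not say who is masked, and 5.1 foresees reporting emergency unblinding, so some masking exists.
- *That all diagnoses are counted regardless of visit.* The source of events is not stated.
- *That RUTF versus MNP is biased in a known direction.* Both arms receive a supplement.
- *That the primary endpoint is affected.* Nothing in the SAP says whether it is recorded at unscheduled visits.

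**Conclusion.** The point holds in a limited form. The event that releases a supplement course in two arms is also the counted morbidity outcome, and controls have no matching incentive. Comparisons of each supplement with control on the event count and on the proportion newly diagnosed may therefore be biased against the supplements.

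The size cannot be derived from the SAP. Under the assumption that all episodes are self-presented, an ascertainment ratio of 1.11 hides a true rate ratio of 0.90, and 1.25 hides 0.80. If half of the episodes come from scheduled visits without a differential, hiding 0.80 takes a ratio of 1.5. Modest differences in attendance would thus be enough to matter for modest effects. The planned analysis would neither correct the distortion nor reveal it. The consequence is confined to what may be concluded about morbidity against control.

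**What to change.** Keep the all-visit count as the morbidity analysis, and add to section 5.5:

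1. A sensitivity analysis of both morbidity endpoints restricted to study-disease diagnoses made at scheduled visits.
2. For each arm, the number of self-initiated attendances and the number of diagnoses by visit type (scheduled or self-initiated).
3. A statement that an effect on disease incidence against control will not be concluded from the all-visit count alone if attendance differs by arm or if the two analyses disagree.

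Treatment, sample size and the supplement rule do not change. The cost is a visit-type flag in the analysis data and a little more analysis work. The added analysis has fewer events and the limits named under the objection. It removes the attendance component but not any discretion in diagnosis, so it should be read beside the all-visit result and not in place of it.

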### **3 Endpoints**

#### **3.1 Primary endpoint**

The primary endpoint is “negative nutritional outcome (NNO)” of a child within the 6 months follow-up period. The incidence of a negative nutritional outcome will be defined in two different ways according to the baseline nutritional status:

- for children with no malnourishment at time of entry into study, “negative nutritional outcome” is defined as progression to moderate or severe malnourishment,
- for children with moderate malnourishment at time of entry into study, “negative nutritional outcome” is defined as loss of  $\geq 10\%$  of baseline weight or progression to severe malnourishment, whichever is reached first.

Thus, the event of a child reaching a “negative nutritional outcome” at least once within 6 months of follow-up period will be compared between the three study groups.

#### **3.2 Secondary endpoints**

Secondary endpoints include

- Number of NNO’s per study group in a period of 6 months
- Time to NNO
- Number of new events of a study disease in 6 months
- Weight change at 14 days and 28 days after study inclusion, and at end of study period
- Rate of weight change (grams/kg/day) at 14 days and 28 days after study inclusion, and at end of study period
- Proportion of children not gaining weight (including losing weight), measured at day-14 and day-28 after study inclusion.
- Proportion of children developing bilateral oedema, overall and per month
- Proportion of moderate acutely malnourished children improving to a non acutely malnourished state, overall and per month
- Mortality: overall mortality
- Morbidity, including the three study diseases (proportion of children with newly diagnosed diseases), overall and per month
- Proportion of children with a reported cough at clinical visit, overall and per month
- Proportion appetite categories
- Proportion and time pattern of children who were breast-fed at baseline and stopped being breast-fed during the study

#### **3.3 Safety measures**

- Serious adverse events
- Serious adverse reactions

### **4 Populations for analysis**

#### **4.1 Intention to treat population**

The intention to treat population (ITT) includes all patients randomised that received at least one dose of study medication and who have baseline data recorded.

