## **4.4 Baseline drop-out**

All patients enrolled who dropped out before the start of randomized treatment.

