### 5.3 Primary analysis of primary endpoint

The primary endpoint is “negative nutritional outcome” of a child within the 6 months follow-up period. The incidence rate (in formulae below referred to simply as ‘rate’) of “negative nutritional outcome” will be computed as the number of events divided by total observed person-time in each treatment group. As an “event” the first time a child reaches a negative nutritional outcome will be used. The primary analysis of the primary endpoint will be performed on the intention to treat population with no imputation of missing data.

In the primary analysis, RUTF will be compared to the control group

The hypotheses in this step are

$$H_0: \text{rate}_{\text{RUTF}} = \text{rate}_{\text{Control}}$$

vs.

$$H_1: \text{rate}_{\text{RUTF}} \neq \text{rate}_{\text{Control}}$$

where  $\text{rate}_{\text{RUTF}}$  = rate of “negative nutritional outcome” in the children in the RUTF group, and  $\text{rate}_{\text{Control}}$  = rate of “negative nutritional outcome” in the children in the control group.

The comparison of rates among the two treatment groups (RUTF vs. control) will be performed by a Poisson regression model, adjusted for nutritional status at enrolment (fixed effect) and will be performed within one model including the three intervention groups with contrasts for each two-group comparison. The result will be presented as rates for each intervention group, and a rate ratio for the pair-wise comparison (each with 95% confidence intervals). Tests will be two-sided with a significance level of 0.05.

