The general problem of assay sensitivity in non-inferiority comparisons can be addressed in this study by the 3-arm design including a control group receiving no nutritional supplementation. Thus, superiority of the two nutritional interventions (RUTF and MNP) versus no intervention can be evaluated prior to the non-inferiority comparison.

These step-wise comparisons of rates among treatment groups will be performed by the same Poisson regression model, adjusted for nutritional status at enrolment (fixed effect) as described above, i.e. performed within one model including the three intervention groups with contrasts for each two-group comparison. The results will be presented as rates for each intervention group, and rate ratios for the pair-wise comparison (each with 95% confidence intervals).

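### The set labelled intention to treat carries a dosing condition that is undefined for a control arm given no supplement, and on any reading it excludes children after randomisation

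*SAP*

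**What the plan says.** SAP section 4.1 defines the intention-to-treat population as one that "includes all patients randomised that received at least one dose of study medication and who have baseline data recorded". It contains no arm-specific wording, and study medication is not defined anywhere in the SAP.

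Section 2 describes group C as: "Be included in a control group receiving standard care and treatment but not receiving nutritional supplementation (control group". Section 5.4.1, on assay sensitivity, again speaks of a design "including a control group receiving no nutritional supplementation". No placebo is mentioned, and section 2 calls the trial partially blinded.

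Section 5.3 states: "The primary analysis of the primary endpoint will be performed on the intention to treat population with no imputation of missing data". The comparison run on that set is explicit: "In the primary analysis, RUTF will be compared to the control group".

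Section 4.4 defines baseline drop-outs as "All patients enrolled who dropped out before the start of randomized treatment", without saying when randomised treatment starts for a control child.

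**The concern.** An intention-to-treat set protects the comparison because membership is settled at randomisation. A condition on receiving a dose is settled afterwards. Such a condition is sometimes defended on the ground that it acts alike in every arm. That defence is not available if one arm has no dose to receive.

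A child allocated to RUTF or MNP who receives none (because of refusal, illness or a caregiver leaving, for example) would be removed, while a similar child allocated to control would stay. With no placebo mentioned, families can presumably see whether they were given a supplement, so not starting may depend on the allocation.

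The definition also reaches beyond the primary test. The per-protocol set is a subset of this one (section 4.2), the sensitivity analysis for missing data uses it (section 5.4.4), and the secondary endpoints use these two sets (section 5.5). No planned efficacy analysis includes all randomised children.

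**Working it through.** **Step 1: are controls in the set?** They have to be. Section 5.3 compares RUTF with control on the intention-to-treat set. Section 4.2 draws the per-protocol set from it and then applies one exclusion criterion explicitly to all three groups, control included.

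**Step 2: how can the dosing condition be applied?** The term is undefined, so two readings remain.

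| Meaning of study medication | Controls | RUTF and MNP children without a dose | Result |
|---|---|---|---|
| The supplement | Exempted by an unwritten rule | Removed | Exclusion after randomisation in two of three arms |
| The standard medical treatment given to all arms | Removed if untreated | Removed only if untreated | Exclusion after randomisation in all arms |

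Neither row is intention to treat. The first also breaks the symmetry of the primary comparison. The SAP does not say which row is meant.

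**Step 3: how large could the effect be?** The SAP gives no number of never-dosed children and no event rates, so there is no stated figure to reproduce and the bias cannot be computed. The following is an illustration with assumed inputs, for the first row of the table:

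- True rate ratio, RUTF to control: 1.00.
- Fraction of children who never start, or would not have started if allocated to supplement: f = 0.02 to 0.05.
- Their event rate: 2r, against r for all other children.
- All are followed as long as the others.

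Control arm, with everyone kept: R = f × 2r + (1 − f) × r = r(1 + f).

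RUTF arm, with non-starters removed: r.

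Apparent ratio = r / [r(1 + f)] = 1 / (1 + f).

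- f = 0.02: 1 / 1.02 = 0.980
- f = 0.05: 1 / 1.05 = 0.952

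**Step 4: what changes the result?** If non-starters have k times the rate of the others, the ratio is 1 / [1 + f(k − 1)]. It is below 1 when k > 1, equal to 1 when k = 1 and above 1 when k < 1, so the direction depends on a prognosis that the SAP does not document.

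Follow-up matters too. Section 5.3 uses observed person-time without imputation. An active-arm child lost at once adds no events and no person-time under either definition, so excluding that child changes nothing. With partial follow-up, the shift caused by the definition lies between zero and the figures above.

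**The case against.** A reader might infer that the rule empties the control arm, since no control child receives a supplement. The SAP does not support that as a real outcome: sections 4.2 and 5.3 both presuppose controls in the set.

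Three further arguments reduce the concern:

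- **The term may cover standard treatment.** Elsewhere the SAP speaks of supplements and sachets rather than medication, all arms receive standard care and treatment, and control is counted among the treatment groups (sections 5.1 and 5.3). On this reading the one-sidedness disappears. The reading is possible but nowhere stated, and the exclusion would still follow randomisation.
- **Received may mean dispensed.** Where section 4.2 means ingestion, it refers to what the child took or consumed. Section 2 also provides supplement at each new qualifying episode, and section 4.1 does not tie the dose to the first one. Few children may therefore be excluded. That limits the likely size but does not settle the rule.
- **The bias figures rest on assumptions.** This stands. The 2% to 5%, the doubled risk and the complete follow-up have no source in the SAP.

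The point on section 4.4 is minor. The category is descriptive, no stated analysis uses it, and randomised treatment could be read to include allocation to standard care.

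**Conclusion.** The concern holds as a defect of definition in the primary analysis population. Section 4.1 attaches to a set called intention to treat a dosing condition whose application to controls is not stated. The likely application is a one-sided post-randomisation exclusion from the RUTF and MNP arms; the alternative is a post-randomisation exclusion in all arms. This conclusion needs no numerical assumption.

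The possible distortion is a separate matter. The range of about 0.98 to 0.95 for a true ratio of 1.00 is an illustration that holds only under the inputs listed, and early loss of non-starters would shrink it. A reader might also infer that the rule is shown to favour RUTF. It is not: that direction requires non-starters to have a worse prognosis, which is plausible but undocumented. The case for changing the text is that the rule cannot be carried out as written without an undocumented choice, and that choice should not be left until the data are seen.

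**What to change.** - **Section 4.1:** define intention to treat as all randomised children with a recorded baseline nutritional status, analysed in the allocated group regardless of any supplement received, with person-time counted from randomisation. The baseline condition can stay in this form because nutritional status at enrolment is the covariate in the section 5.3 model, and it can apply equally to every arm.
- **Dose-based restrictions:** keep them in the per-protocol set, which already has intake criteria, or in a separately labelled sensitivity set.
- **Section 4.4:** word baseline drop-out by the date of randomisation in all three arms.

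The cost is a change of SAP wording, with no additional visits or data collection. The downside is that a few children who never started supplement enter the primary analysis and may slightly dilute the estimated effect.
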